### c. OUTCOME MEASURES

#### **Primary**

1. Cumulative incidence of PCC at 3 months in children who tested COVID-19 positive (PCR, or RAT), and the proportion with PCC at 6 and 12 months post-infection will be assessed from survey responses and follow-up.

#### **Secondary**

1. Incidence of PAS at 3 months in children following influenza (PCR or RAT) and the proportion with PAS following influenza at 6 and 12 months post-infection from survey responses and follow-up
2. The relative risk comparing the cumulative risk of meeting the case definition for PCC among participants with COVID-19 to the cumulative risk of meeting the case definition for PAS among participants with influenza from survey responses and follow up.
3. A multivariable logistic model will be developed for predicting PCC at 3 months, incorporating pre-specified predictors such as age (treated as continuous), sex, pre-existing conditions, and socioeconomic status.
4. Difference in the quality of life of children and adolescents (aged 2-18) using the Pediatric Quality of Life Inventory (PedsQL) short form (scores 0-100) in the following groups:
  - PCC compared to those without PCC in COVID-19-positive cases.
  - PAS compared to those without PAS in influenza-positive cases.
  - PCC compared to those with PAS
5. Difference in fatigue of children and adolescents (aged 2-18) at 3, 6, and 12 months using the PedsQL Multidimensional Fatigue Scale (scores 0-100), in the following groups:
  - PCC compared to those without PCC in COVID-19-positive cases.

- PAS compared to those without PAS in influenza-positive cases.
  - PCC compared to those with PAS
6. Difference in school absenteeism in the previous month at 3, 6, and 12 months from the self-reported survey, in the following groups:
    - PCC compared to those without PCC in COVID-19-positive cases.
    - PAS compared to those without PAS in influenza-positive cases.
    - PCC compared to those with PAS
  7. The difference in vaccine uptake (confirmed using the Australian Immunisation Register) in those with PAS compared to those without PAS in influenza-positive cases.
  8. Proportion of participants meeting the case definition for PCC at 3 months following COVID-19 infection, by infection history (first infection vs. reinfection).
  9. Description of the duration and type of PCC in those with COVID-19 infections. Derived from 3, 6, and 12 month survey responses.
  10. Description of the duration and clinical features of PAS in children and adolescents following influenza infection. Derived from 3, 6, and 12 month survey responses.

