Follow-up studies on MIS-C indicate that the majority of patients recover fully, including improvement of cardiac dysfunction. Some have suggested that PCC in children is a subclinical presentation of MIS-C. However, elevated markers of inflammation, a central feature of MIS-C, are uncommon in long COVID. Furthermore, there is limited evidence that immunomodulatory treatment, which is very effective in managing MIS-C, has a role in treating long COVID. There are some studies on low-dose naltrexone (LDN) that suggest some patients experience fewer number of symptoms, and improved clinical symptoms, however randomised placebo controlled trials are required. LDN can act as an immunomodulator in multiple autoimmune diseases and malignant tumors. Given the distinct differences between children and adults with COVID-19 infection, paediatric-specific research on PCC is essential.

In September 2022, a panel of 27 experts convened to establish a clinical case definition for the post-COVID-19 condition in children and adolescents, informed by the scientific data available at that time. This definition is expected to undergo revisions as further high-quality evidence emerges and our collective understanding of the condition deepens. The World Health Organization (WHO) defines PCC, as:

- Occurring in individuals with a history of confirmed or probable SARS-CoV-2 infection
- Symptoms last at least 2 months, initially occurring within 3 months of acute COVID-19
- Symptoms generally impact everyday functioning, such as changes in eating habits, physical activity, behaviour, academic performance, social functions (interactions with friends, peers, and family) and developmental milestones.
- Symptoms may be new onset following initial recovery from an acute COVID-19 episode or persist from the initial illness.
- They may also fluctuate or relapse over time.
- Workup may reveal additional diagnoses, but this does not exclude the diagnosis of post-COVID-19 condition.
- More frequently reported symptoms in children compared with controls are fatigue, altered smell/anosmia and anxiety. Other symptoms have also been reported.
- This definition can be applied to children of all ages, with age-specific symptoms and impact on everyday function considered.

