#### **Secondary objectives**

1. Describe the cumulative incidence of influenza infections in children and adolescents at 3 months, and the proportion with ongoing symptoms at 6 and 12 months post-infection.
2. Estimate the relative risk of developing PCC following COVID-19 compared to PAS following influenza at 3 months post-infection.
3. Establish a model for predicting the development of PCC in children and adolescents with COVID-19.
4. Estimate the difference in the quality of life of children and adolescents (aged 2-18) at 3, 6, and 12 months post-infection in the following groups:
  - PCC compared to those without PCC in COVID-19-positive cases.
  - PAS compared to those without PAS in influenza-positive cases.
  - PCC compared to those with PAS
5. Estimate the difference in fatigue of children and adolescents (aged 2-18) at 3, 6, and 12 months post-infection in the following groups:
  - PCC compared to those without PCC in COVID-19-positive cases.
  - PAS compared to those without PAS in influenza-positive cases.
  - PCC compared to those with PAS
6. Estimate the difference in school absenteeism at 3, 6, and 12 months following infections in the following groups:

- PCC compared to those without PCC in COVID-19-positive cases.
  - PAS compared to those without PAS in influenza-positive cases.
  - PCC compared to those with PAS
7. Estimate the difference in influenza vaccine uptake in children and adolescents with PAS following influenza compared to vaccination uptake in those without PAS following influenza.
  8. Estimate the cumulative incidence of PCC in those with COVID-19 re-infections compared to those with first infection at 3 months, and the proportion with ongoing symptoms at 6 and 12 months post-infection.
  9. Describe the duration and clinical features of PCC in children and adolescents with COVID-19 infection.
  10. Describe the duration and clinical features of PAS in children and adolescents following influenza infection.

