#### **Baseline data (1 month after swab result or hospital discharge)**

- Name of person filling in the questionnaire and relationship with the case.
- Sex/gender

- Ethnicity
- Medically diagnosed conditions prior to respiratory infection
- Symptoms of acute COVID-19 infection (first 14 days)
- History of confirmed SARS-CoV-2 tests

Collected by study staff:

- Vaccination history (confirmed on the Australian Immunisation Register)
- If hospitalised (from EMR):
  - Length of stay
  - Number of viral infections
  - Treatment, e.g., antivirals, antibodies
  - Pneumonia Y/N
  - ICU/HDU admission Y/N
  - Respiratory support Y/N

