### b. EXCLUSION CRITERIA

- 1) Inability to give informed consent
- 2) No mobile phone number
- 3) Children and adolescents who are under the care of the statewide WCHN Palliative care service

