### c. STATISTICAL METHODS TO BE UNDERTAKEN

Analyses will follow a pre-specified statistical analysis plan. The cumulative incidence of PCC following COVID-19 (primary objective) and PAS following influenza will be estimated at 3 months post-infection, with 95% confidence intervals. The proportion of individuals with ongoing symptoms will be reported descriptively (n, %) at 6 and 12 months. The relative risk of developing PCC following COVID-19 versus developing PAS following influenza (objective 2) will be estimated using a log-binomial model. A multivariable logistic model will be developed for predicting PCC at 3 months (objective 3), incorporating pre-specified predictors such as age (treated as continuous), sex, pre-existing conditions, and socioeconomic status. Model performance will be evaluated using the area under the receiver operating characteristic curve, with internal validation by bootstrap resampling in line with TRIPOD recommendations. The relatively small expected number of PCC events may limit the number of predictors that can be incorporated into the final model and hence its predictive accuracy. Linear and negative binomial mixed-effects models will assess differences between comparator groups over time in continuous (PedsQL quality of life and fatigue scores, objectives 4 and 5) and count (days absent, objective 6) outcomes, respectively. Log binomial models will compare the risk of developing PAS according to influenza vaccine uptake (objective 7) and the risk of PCC by COVID-19 reinfection (objective 8). The duration and clinical features of PCC and PAS will be described using summary statistics, with summaries at 3, 6 and 12 months. Descriptive analyses will be based on complete case data.

Handling of follow-up and missing data.

Outcomes will be summarised at the planned 3, 6 and 12-month assessments. Participants contribute data to each analysis for which follow-up information is available. For the primary objective, participants with PCC at 3 months who discontinue or miss assessments at 6 or 12 months will be treated as missing for whether symptoms were ongoing at these time-points. Multiple imputation may be considered for the prediction model, depending on the amount and reasons for missing data at 3 months when determining PCC.

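### Outcome 8 takes PCC status at 3 months without separating PCC already present before the index infection, so under equal per-infection risk the reinfection risk ratio is biased upward

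*Protocol*

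**What the plan says.** In the protocol, Section 4.b, secondary objective 8 is to "Estimate the cumulative incidence of PCC in those with COVID-19 re-infections compared to those with first infection at 3 months". Section 4.c turns this into the "Proportion of participants meeting the case definition for PCC at 3 months following COVID-19 infection, by infection history (first infection vs. reinfection". Section 8.c adds only that a log-binomial model will compare "the risk of PCC by COVID-19 reinfection (objective 8"; it names no at-risk set.

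The only case definition in the document is the WHO one, in the literature review (Section 3.c). Three of its elements matter here:
- the infection requirement: "Occurring in individuals with a history of confirmed or probable SARS-CoV-2 infection";
- the timing: "Symptoms last at least 2 months, initially occurring within 3 months of acute COVID-19";
- the course: "Symptoms may be new onset following initial recovery from an acute COVID-19 episode or persist from the initial illness".

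It also allows symptoms to fluctuate or relapse.

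Section 6.b has three exclusions: inability to consent, no mobile phone number, and "Children and adolescents who are under the care of the statewide WCHN Palliative care service". Existing PCC is not among them.

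On data, Section 5.c places the baseline survey 1 month after the swab result or hospital discharge. It lists medically diagnosed conditions before the infection and "History of confirmed SARS-CoV-2 tests". The follow-up surveys ask about symptoms since the previous survey.

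**The concern.** A cumulative incidence counts new cases among children free of the condition at time zero. Outcome 8 counts children who meet the definition at 3 months. The two agree for a true first infection, because such a child cannot bring PCC from an earlier one. They need not agree for a reinfection: a child whose earlier PCC has not resolved has a history of infection, has persisting symptoms and had onset within 3 months of an acute episode, though not necessarily the index one. As worded, one group can hold old and new cases and the other only new ones.

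This goes beyond what a statistical analysis plan could settle alone. An attribution rule written later needs data on whether symptoms were already present before the index infection. The items listed in the protocol supply that only for diagnosed conditions.

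Reinfection is a stated motivation for the study (Section 3.c), and the results are meant to inform vaccine recommendations. A ratio raised by carried-over cases could be read as a reinfection effect.

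**Working it through.** **The plan's own figures.** The protocol gives no effect size or power for objective 8. Its one computed figure, in Section 8.b, is a precision of 0.62% to 1.47% at incidences of 1% and 6%. The half-width 1.96 × √(p(1 - p)/n) with n = 1,000 gives 0.617% and 1.472%, so these reproduce. With 1,222 × 0.8 = 978 children they are 0.624% and 1.488%.

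**Inputs.**
- r, the PCC risk per infection: 1% to 6% (Section 8.b), taken as equal in both groups; this is the null.
- s, the share of earlier PCC still present at the 3-month assessment after reinfection: not in the documents. Assumed 10%, 25% and 50%. Section 3.b says only that burden can last up to 12 months.
- Analysed number: 978, from 1,222 less 20%.
- Reinfected share: not in the documents. Assumed one half, so 489 per group.

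**Expected ratio under the null.** The first-infection proportion is r. With carry-over and new PCC independent, the reinfected proportion is rs + (1 - rs)r. Dividing by r gives RR = 1 + s(1 - r). For r = 6% and s = 50%: 0.03 + 0.97 × 0.06 = 0.0882, and 0.0882/0.06 = 1.47.

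| s | r = 1% | r = 3% | r = 6% |
|---|---|---|---|
| 10% | 1.10 | 1.10 | 1.09 |
| 25% | 1.25 | 1.24 | 1.24 |
| 50% | 1.50 | 1.49 | 1.47 |

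The direction does not need independence: the probability of carried-over or new PCC is never below that of new PCC alone. If children with PCC still present are removed from the risk set, the expected ratio is 1.00 for every r and s.

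**Chance that the 95% CI excludes 1 under this null.** A normal approximation on log RR with 489 per group gives:

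| s | r = 1% | r = 3% | r = 6% |
|---|---|---|---|
| 10% | 5.3% | 5.8% | 6.5% |
| 25% | 6.6% | 9.6% | 14.2% |
| 50% | 10.6% | 22.2% | 38.6% |

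The r = 1% column is rough, since 489 × 0.01 is about 5 events in the first-infection group.

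**Primary incidence.** With half reinfected and r = 6%, the pooled proportion is (6.00 + 7.41)/2 = 6.7% at s = 25% and (6.00 + 8.82)/2 = 7.4% at s = 50%.

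**The case against.** The strongest reply is that no sentence says carried-over PCC is counted. Outcome 8 speaks of 3 months following infection, objective 8 speaks of cumulative incidence, and the onset window can be read as running from the index episode. The WHO definition appears in a literature review, the operational rule may be in the analysis plan, and the survey follows an ISARIC instrument that is not shown. Table 1 also marks physical and mental health symptoms and medical history at baseline. This stands to the extent that the counting is inferred from silence. It does not remove the point: nothing in the text fixes the index-episode reading. The listed baseline is taken after the infection, and no listed item dates undiagnosed symptoms relative to it.

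A reader might infer that the ratio exceeds 1 even if reinfection adds no risk. The documents do not support that. If reinfection caused no PCC at all, the ratio would equal s, which is below 1. The upward bias holds against a null of no more risk than a first infection, with comparable groups; differences in age, vaccination or immunity could offset it.

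A reader might also infer that the recorded first-infection group is free of earlier PCC. Only confirmed tests are recorded, while the definition admits probable infection. Some recorded first infections may be reinfections, which would dilute the bias.

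The size is also open to challenge. The relevant persistence runs to the 3-month assessment, not merely to the moment of reinfection, which relapses aside can only make s smaller. At s = 10% the error rate is close to the nominal 5%. Even at s = 50%, the shift in a 6% primary incidence (about 1.4 percentage points) lies within the stated 1.47% margin.

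**Conclusion.** The point holds in a limited form. Outcome 8 does not deliver the cumulative incidence that objective 8 asks for, because it neither excludes nor separates PCC present before the index infection. The definition shown lets such a child count. The relative bias is about s(1 - r), resting on equal per-infection risk, otherwise comparable groups and carried-over PCC being counted. It ranges from near negligible at s = 10% to a ratio of about 1.5 at s = 50%. Both s and the half-reinfected split are assumptions, so the direction under this null is firmer than the size. It deserves correction because the separating question must be in the survey before the data are collected. The effect on the primary incidence is secondary and calls for a sensitivity analysis only.

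**What to change.** - In outcome 8 and Section 8.c, tie PCC to the index infection: count only symptoms that began, or clearly recurred anew, after the index swab.
- Limit the objective 8 comparison to children without ongoing PCC at that swab, and report carried-over PCC separately.
- Give the primary incidence with and without children who carry earlier PCC, as a sensitivity analysis.
- Add one baseline item on whether each ongoing symptom was already present before the current infection and, if so, whether it followed an earlier COVID-19 infection. Ask it of all COVID-19 participants regardless of infection history. Put only to reinfected children, it could remove those with any lingering symptom from one group alone and push the ratio down.

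The cost is one survey item, reliance on parental recall about 1 month after the swab, and a slightly smaller objective 8 denominator.

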## 5. STUDY DESIGN

### a. STUDY TYPE & DESIGN & SCHEDULE

This study is designed as a longitudinal cohort study. The study will recruit participants for 24 months from study commencement, and each participant will be enrolled for 12 months.

### b. STANDARD CARE AND ADDITIONAL TO STANDARD CARE PROCEDURES

Standard care for individuals under 18 years of age who experience ongoing sequelae from a COVID-19 infection or non-COVID respiratory infections primarily involves assessment through general practice or hospital outpatient services. All children who report severe persistent symptoms who have not yet undergone a medical assessment with functional impairments (WHO definition) will be contacted for a Nurse-led or WCHN employed Paediatrician via a telehealth call to further clinically assess cases and determine if a referral to their General Practitioner is required. Refer to Appendix B for details regarding Nurse-led or WCHN employed Paediatrician follow up process. South Australia does not have a specialised long COVID clinic or management protocol for children and adolescents.

### c. STUDY METHODOLOGY

The Vaccinology and Immunology Research Trials Unit conducts surveillance of SARS-CoV-2, and influenza infections at the Women's and Children's Hospital as part of the Paediatric Active Enhanced Disease Surveillance (PAEDS) network.

Similar to current methods used by the PAEDS network, for phase 1 of the study WCHN pathology results will be searched each fortnight by a WCHN employed level 2 Registered Nurse, and SARS-CoV-2 test-positive and influenza test-positive children and adolescents (aged 0-18 years) will be invited to participate (Figure 1).

For phase 2 of the study, SARS-CoV-2, and influenza infections will be recruited from SA Health notifications of PCR or Rapid Antigen Tests (RAT), to ensure the results are generalisable to the South Australian populations and include children and adolescents with potentially milder acute illness. Once recruitment commences through SA Health notifications, this will replace invitations sent from WCHN to avoid duplication of invitations.

COVID-19 and influenza cases parents will be sent an SMS invitation, and if they consent, agree to 1) completing a baseline survey, then surveys at 3, 6, and 12 months, 2) for the research team to review EMR if they present to a SA Health hospital (WCHN, FMC, and LMH), and permission for the study team to access the Australian Immunisation Register to check COVID-19, and influenza immunisation status.

To reimburse participants for their time and encourage the completion of surveys, a \$10 online supermarket voucher will be provided upon completion of the initial, then 3, 6, and 12-month surveys for their time (\$40 in total). If parents deem that their 12-18-year-olds are mature enough to understand the relevant information and to give consent, assent will also be collected if they wish to complete the surveys themselves. If the 12-18 year old does not agree to participate from the study, they will be withdrawn from the study.

[figure not shown]

**Figure 2: Recruitment flow chart for WCHN (Phase 1 of recruitment)**

[figure not shown]

**Figure 3: Recruitment flow chart for SA Health notifications (Phase 2 of recruitment)**

#### Data collection (Phase 1 of WCHN recruitment)

Following a waiver of consent, basic baseline information of all COVID-19 and influenza cases presenting to a WCHN site will be collected by a WCHN employed level 2 Registered Nurse from EMR to provide baseline denominator data for those not enrolled in the study. Their name and phone number are also required to send the initial invitation. This information will include:

- Name
- Date of birth
- Phone number
- Swab date
- Postcode
- Type of positive test
- Admitted to hospital Y/N
- Presentation for respiratory illness (Y/N)
- Discharge status

#### Data collection (Phase 2 of Communicable Disease Control Branch [CDCB] recruitment)

The Disease Surveillance and Investigation Section at the CDCB routinely collects notification data for influenza and COVID-19. No additional data will be collected, and notification data will not be shared with the WCHN study team. CDCB will only provide the WCHN study team with the aggregated number of SMS invitations sent for influenza and COVID-19.

The SMS invitation will contain a link to the participant information sheet and consent form, which are securely stored on a RedCap database housed on the CALHN server and managed by the WCHN study PI. The WCHN study team will only have access to information from individuals who have provided consent.

#### Data from consented participants

Following consent, survey data will be collected from those enrolled using an online RedCap baseline questionnaire to be completed at recruitment, followed by questionnaires at 3, 6, and 12 months post-infection. The WCHN study team will validate the positive test results of consented participants with CDCB. Questionnaires will be available for parents/carers or participants to answer where applicable. Quality of life questions will be available in two of the fastest-growing non-English languages used at home in South Australia: Mandarin, and Vietnamese. The survey is based on the International Severe Acute Respiratory and Emerging Infection Consortium (ISARIC) COVID-19 Paediatric follow-up protocol and questionnaire. If there is no response from a survey after one week, 2 reminders will be sent a week apart. Data will be collected using a secure password-protected web application housed on a SA Health data server (RedCap).

Data to be collected includes:

